# Comparison of traditional and upper thoracic epidural analgesia after off‐pump coronary artery bypass graft surgery: A Quasi‐experimental study

**DOI:** 10.1002/hsr2.774

**Published:** 2022-08-10

**Keywords:** conventional analgesia, off‐pump coronary artery bypass graft, pain, thoracic epidural analgesia, VAS

## Abstract

**Background and Aims:**

Surgical trauma initiates changes in central and peripheral nervous systems that need to be treated therapeutically to facilitate postoperative pain. The quality of postoperative analgesia is expected to affect clinical outcomes positively. Albeit optimal pain relief following cardiac surgery is often complex, researchers have tried to explore several techniques other than conventional ones during the last decade to find a unique analgesic method for postcardiac surgical patients. This study aims to find a unique analgesic approach that maximizes patient satisfaction after off‐pump coronary artery bypass graft (OPCABG) surgery.

**Methods:**

The current study will compare the analgesic effect of upper thoracic epidural analgesia (TEA) with conventional analgesia after OPCAB graft surgery. For this, we will use a Quasi‐experimental study design. Patients admitted for coronary artery bypass graft (CABG) surgery will be assigned into two groups. The control group (conventional) will receive intravenous opioids and nonsteroidal anti‐inflammatory medications, and the study (case) group (TEA) will receive Inj. Bupivacaine 0.25% as an infusion through the epidural catheter. Physiologic parameters like hemodynamic and respiratory variables and pain scores will be recorded in predesigned format periodically.

**Results:**

We expect to analyze a total of 130 consecutive off‐pump CABG surgery patients in Group A (Case, 65 patients) and Group B (Control, 65 patients). Study variables will be the visual analog scale score, hemodynamic parameters (heart rate, mean arterial pressure, and respiratory parameters (respiratory rate, PaO_2_, PaCO_2_, PEFR, FEV_1_). After data collection, the result will be analyzed and published in the public domain and in journals.

**Conclusion:**

We expect thoracic epidural analgesia with local anesthetics will be a reliable postoperative analgesic option.

## INTRODUCTION

1

Postoperative pain control improves clinical outcomes and patient satisfaction as well as lowers pain scores after cardiac surgery. The quality of postoperative analgesia positively affects morbidity in cardiac surgery.^1^ Thoracic epidural analgesia (TEA) is a valuable tool for acute pain relief for both anesthesiologists and surgeons. Hoar et al. first described the use of TEA for patients having heart surgery in the modern surgical era.^2^ Subsequently, thoracic epidural anesthesia and analgesia have been used to manage patients having cardiac, thoracic, and upper abdominal procedures during and after surgery.^3^, ^4^

Off‐pump coronary artery bypass graft (OPCABG) is a commonly practiced procedure for ischemic heart disease worldwide.^2^, ^3^, ^4^ For the first time in Bangladesh, [name] [name] and his team performed OPCAB surgery using epidural anesthesia on March 9, 2006 in a private hospital in Dhaka, which opened a new era on the horizon of cardiac surgery in Bangladesh which facilitated epidural analgesia in cardiac surgical patients.^5^

International Association for the Study of Pain (IASP) defined pain as “An unpleasant sensory and emotional experience associated with or resembling that associated with, actual, or potential tissue damage.”^6^ Postoperative pain stimulates the sympathetic nervous system and increases myocardial oxygen consumption. Oxygen supply‐demand mismatch can lead to myocardial ischemia, detrimental to patient outcomes.^7^, ^8^ Optimal postoperative pain management with a regular and routine assessment of pain will improve postoperative outcomes. The patient's assessment of pain using a visual analog scale (VAS) is the most reliable and should be used when possible.^9^

Traditionally opioids, nonsteroidal anti‐inflammatory medications (NSAIDs), or a combination of both, are being used to provide analgesia following cardiac surgery, which is linked to adverse side effects.^10^, ^11^ Longer‐acting opioids, such as morphine, delayed postoperative tracheal extubation due to drowsiness and respiratory depression. Concerns about adverse events NSAIDs include altered stomach mucosal barrier, renal tubular function, and platelet aggregation inhibition, limiting their usage in cardiac surgery.^12^

Despite many new methods, advanced pharmacological analgesic preparations, and proven pain services, postoperative pain control in coronary artery bypass graft (CABG) surgery has remained a challenge. As a general rule, single‐modality therapy is often recommended to treat immediate postoperative pain.^10^, ^11^, ^12^, ^13^ In the current era of early extubation (fast‐tracking), cardiac anesthesiologists are investigating novel options for adequate analgesia in patients undergoing cardiac surgery that are not traditional opioids and NSAIDs.^1^, ^14^

This current study will aim to evaluate an effective method of optimum postoperative analgesia using either TEA (Inj. Bupivacaine 0.25% at 3–5 ml/h continuous infusion) or conventional analgesia (intravenous Ketorolac 30 mg 08 hourly with or without narcotic analgesic) after OPCAB surgery. Furthermore, we also aim to evaluate postoperative cardiac and respiratory variables in relation to pain intensity after OPCAB surgery.

### Research hypothesis

1.1

#### Null hypothesis (H_0_)

1.1.1

There is no significant difference between conventional and upper TEA in pain control after OPCAB surgery.

#### Alternative hypothesis (H_a_)

1.1.2

Upper TEA with Inj. Bupivacaine will provide better postoperative analgesia than conventional one after OPCAB surgery.

### Research gap

1.2

Researchers explore significant pain control after cardiac surgery using different methods (e.g., local infiltration, intercostal and paravertebral blocks, spinal and epidurals, patient‐controlled analgesia) of pain services compared to conventional ones. Furthermore, an effective single modality of analgesia has yet not been established.

There is seldom a study performed in Bangladesh to explore the role of epidural analgesia after off‐pump CABG. So, the research gap is to find an effective analgesia method after OPCAB surgery using TEA. We characterize the research gap with the PICO framework as follows:

*Population* (*P*): Patients admitted for scheduled OPCAB surgery.

*Intervention* (*I*): TEA using Inj. 0.25% Bupivacaine as a continuous infusion pump.

*Comparison* (*C*): Traditionally used opioids and NSAIDs (Inj. Ketorolac 30 mg iv) analgesics.

*Outcomes* (*O*): Improved postoperative analgesia and reduced postoperative morbidity.

### Conceptual framework

1.3

Early extubation and hemodynamic stability are the primary concerns of cardiac anesthesiologists in the modern era of fast‐tracking. The analytical framework (Diagram 1) for this study has been created based on the study's objective. The primary aim of this study is to find an efficient and reliable analgesic approach following OPCAB surgery.

**Diagram 1 hsr2774-fig-0002:**
[figure not shown]
Research paradigm illustrating the steps of the current study protocol from population recruitment to final analysis and construction of hypothesis.

## PATIENTS AND METHODOLOGY

2

This Quasi‐experimental Study design will be conducted from February 2021 to July 2022 at the Department of Cardiac Surgery, Bangabandhu Sheikh Mujib Medical University, and Al‐Helal Specialized Heart Hospital, Bangladesh. Patients who will undergo elective off‐pump CABG surgery will be included in the study. The study exclusion criteria are patient refusal or uncooperative patient, abnormal coagulation profile, previous cardiothoracic, cervical, or upper thoracic operation, known case of chronic obstructive pulmonary disease, chronic kidney disease, chronic liver disease malignancy, systemic or local infection, and any spinal abnormality. Also, the patient who converted from OPCABG to On‐pump during the procedure will be excluded from the study.

A total of 130 patients will be evaluated in two groups; Group A (Case 65 patients): off‐pump CABG surgery under general endotracheal anesthesia and will receive postoperative TEA infusion (Inj. Bupivacaine 0.25%); and Group B (Control 65 patients): off‐pump CABG surgery under general endotracheal anesthesia and will receive postoperative conventional analgesia (intravenous Ketorolac 30 mg with or without narcotic analgesics). Study variables will be VAS score, hemodynamic parameters like heart rate, mean arterial pressure, and respiratory parameters (respiratory rate, partial pressure of oxygen_2_, partial pressure of carbon dioxide, peak expiratory flow rate, & forced expiratory volume in the 1st second.

In our study, a continuous response variable, pain score by VAS among two groups, TEA and conventional analgesia among OPCAB patients. In a previous study, within each subject group, responses were generally distributed with a 2.3 standard deviation.^14^ If the actual difference in the two group means of VAS score is 1.0; in that case, we will need to study 65 for TEA and 65 for conventional analgesia in OPCAB patients to reject the null hypothesis with a probability (power) of 0.8 that the population means of the two groups are equal. The probability of Type I error is 0.05 and *Z_α_
* = 1.645 & *Z_β_
* = 0.8416, (as H_a_: µ_a_ > µ_0_) for this null hypothesis test. Therefore, we will need 65 subjects in each group, and the total sample size will be at least 130.

$$n=\frac{2\sigma^{2}}{\Delta^{2}}{\left(Z_{\alpha }+Z_{\beta }\right)}^{2}$$

The above formula used to calculate the sample size is required to compare two groups when the endpoint is quantitative data.^15^, ^16^

### Ethical consideration

2.1

Before starting data collection, informed written consent would be taken from all the respondents. The confidentiality of subjects will be protected by offering assurance to respondents that the information they provide will not be revealed and will only be used for study purposes. Patients will have the right to agree, disagree, or leave the study.

### Statistical analysis

2.2

Statistical analysis will be conducted using Statistical Package for Social Sciences (SPSS) version 25.0 for windows software. The student's *t*‐test will evaluate the continuous data, and categorical data will be evaluated using the *χ*
^2^ test. A *p* ≤ 0.05 will be considered statistical significance.

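### Groups formed without stated randomisation at two hospitals are to be compared by unadjusted tests, so an imbalance between them may be read as an epidural effect

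*Protocol article*

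**What the plan says.** The title, the abstract and section 2 (Patients and Methodology) all call the study quasi-experimental. On allocation, the abstract says only "Patients admitted for coronary artery bypass graft (CABG) surgery will be assigned into two groups". Section 2 places the study at two institutions over 18 months: the quasi-"experimental Study design will be conducted from February 2021 to July 2022 at the Department of Cardiac Surgery", the institutions being "Bangabandhu Sheikh Mujib Medical University, and Al‐Helal Specialized Heart Hospital, Bangladesh". No section of the article mentions randomisation, matching or stratification by hospital.

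The sample size in section 2 is that of a plain comparison of two means: "Therefore, we will need 65 subjects in each group, and the total sample size will be at least 130".

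Section 2.2 (Statistical analysis) fixes the tests. Student's t-"test will evaluate the continuous data, and categorical data will be evaluated using the" chi-square test, with significance at p ≤ 0.05. Neither this section nor any other names a covariate, a hospital term, a regression model or a propensity method.

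The alternative hypothesis in section 1.1.2 is causal: upper epidural analgesia with bupivacaine will give better postoperative analgesia than the conventional approach.

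**The concern.** A two-sample t-test estimates the difference between the groups as they happen to be composed. That difference equals the treatment effect only if the groups would have had the same mean VAS under the same treatment. Randomisation would justify that assumption on average. Here nothing in the stated design does, and the analysis takes no step to replace it.

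The possible sources of imbalance follow from the design itself: two hospitals, an 18-month recruitment window, and an allocation rule that the article does not describe. If epidural patients came disproportionately from one hospital or one period, or differed in prognosis, the t-test would count the resulting VAS difference as an effect of the epidural. The bias could also run the other way. A shift of 0.5 points against the epidural would halve the planned 1.0-point difference. The haemodynamic and respiratory outcomes, which are also continuous, are exposed in the same way, and the chi-square test is equally unadjusted.

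At stake is whether a result at p ≤ 0.05 can be taken as evidence for the causal hypothesis.

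**Working it through.** **Inputs from section 2.** For the SD, "responses were generally distributed with a 2.3 standard deviation". For the planned effect, "If the actual difference in the two group means of VAS score is 1.0". Z_α = 1.645 (one-sided 0.05), Z_β = 0.8416 (power 0.8), 65 per group.

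**Step 1: the plan's own figure.**
n = 2σ²(Z_α + Z_β)²/Δ² = 2 × 2.3² × (1.645 + 0.8416)² / 1.0² = 10.58 × 6.183 = 65.4 per group. The stated 65 reproduces. The formula treats the whole difference in means as the treatment effect.

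**Step 2: standard error of the t-test.**
SE = 2.3 × √(2/65) = 0.403 VAS points.

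**Step 3: false-positive rate under an assumed shift.** Let the true effect be zero and let imbalance shift the difference in means by b. The t statistic then follows a noncentral t distribution with 128 degrees of freedom and noncentrality b/SE. The two-sided 5% critical value is 1.979.

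| Assumed shift b (VAS points) | b/SE | Two-sided rejection rate |
|---|---|---|
| 0 | 0 | 5% |
| 0.25 | 0.62 | 9.4% |
| 0.5 | 1.24 | 23.3% |
| 0.7 | 1.74 | 40.6% |

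On the one-sided basis used for the sample size, a shift of 0.5 in favour of the epidural gives 34%. The shifts are assumptions; the article gives no figure for them.

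**Step 4: how hospital alone could produce such a shift.** Assume that the hospitals differ by 1.0 VAS point in mean pain, and that one hospital supplies share p_A of the epidural group and p_B of the control group. The bias is 1.0 × (p_A − p_B). The rates use the normal approximation.

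| p_A / p_B | Bias | Two-sided rejection rate |
|---|---|---|
| 60% / 40% | 0.2 | 8% |
| 70% / 30% | 0.4 | 17% |
| 80% / 20% | 0.6 | 32% |

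**Step 5: what adjustment costs in precision.** Adding a hospital term multiplies the variance of the group effect by 1/(1 − φ²), where φ is the correlation between group and hospital. With hospitals of equal size, φ = p_A − p_B. Keeping the SD at 2.3 and one-sided alpha at 0.05, power for 1.0 at 65 per group goes from 80% to:

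- φ = 0.2: factor 1.04, power 78%
- φ = 0.4: factor 1.19, power 73%
- φ = 0.6: factor 1.56, power 63%

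If each hospital supplied only one group, φ = 1, the factor is infinite, and the effect cannot be separated from hospital.

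Prognostic covariates pull the other way by reducing residual variance. If they explain 15% or 30% of VAS variance (assumption), two-sided power for 1.0 goes from 0.69 to 0.76 or 0.84, but only when covariates and group are uncorrelated. At φ = 0.6 the same covariates give 0.57 or 0.65, below the unadjusted 0.69.

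**The case against.** The strongest objection is that confounding is possible here but not shown. The article speaks of consecutive patients who are assigned, and nowhere says that patients are picked for an epidural on prognosis. The two diagrams that trace the study procedure are not reproduced in the text at hand, and the article condenses a fuller protocol. Alternation within each hospital, for example, would also be quasi-experimental and would leave little imbalance in hospital or calendar time. This stands. A reader might infer that the t-test will give a biased effect, or that the study could not support its hypothesis at all. The documents do not support either: the bias may be small, and an unadjusted comparison is weaker evidence, not none.

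Second, the exclusions (chronic lung, kidney and liver disease, malignancy, abnormal coagulation, earlier cardiothoracic surgery) remove some prognostic differences. They narrow the population, but they do not balance the groups within it.

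Third, covariate lists and propensity methods are usually left to an analysis plan. That would answer a complaint about missing detail. It does not answer this one, because section 2.2 positively names unadjusted tests for a design that does not suit them.

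Fourth, a reader might expect adjustment to bring a gain in power as well. Step 5 shows that this depends on covariates being balanced between groups, which cannot be assumed here. The case for adjustment rests on bias.

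Finally, a reader might infer that patients still to be enrolled should be randomised. That would change the design and mix two allocation mechanisms, and the stated recruitment period ended in July 2022, although the Data Availability statement calls the project ongoing. It is not part of this point.

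**Conclusion.** The point holds as a mismatch between two things that the article states: a quasi-experimental comparison at two hospitals without stated randomisation, matching or stratification, and unadjusted tests as the comparison behind a causal hypothesis. An imbalance in hospital, calendar time or prognosis may be read as an epidural effect.

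The size is unknown because the allocation rule and the relation of hospital to group are not visible. As an illustration, a shift of half the planned effect would take the two-sided false-positive rate from 5% to about 23%. The range is about 9% to 41% for shifts of 0.25 to 0.7 points. These figures rest on the article's SD of 2.3, 65 per group, no true effect, and the assumed shifts.

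**What to change.** In section 2.2, make the primary VAS analysis a linear model of VAS on group plus hospital, calendar period, age, sex and any other baseline covariates actually recorded, with the list fixed before analysis. For heart rate, mean arterial pressure, respiratory rate, blood gases, PEFR and FEV1, use the same model with the outcome's own pre-operative value where one was recorded. The article lists these as study variables but does not say that they are measured before surgery, so this must be checked first.

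Keep the t-test as a supportive unadjusted result. Report baseline balance by standardised differences. Word the conclusion as an association between epidural analgesia and pain score.

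The cost is revised analysis wording and modest extra analysis work, with four limits to acknowledge. The covariate list can no longer be chosen after seeing results. Unmeasured confounding remains. Precision may fall if hospital or covariates are unbalanced between groups. If each hospital supplied only one group, no model can separate the epidural from the hospital, and the report would have to say so.

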## OPERATIVE DEFINITIONS

3

### VAS

3.1

A VAS is a tool for measuring the pain intensity, which is drawn as 10 cm of a straight horizontal line on a paper, labeled as “no pain at all” and “pain as bad it could be” at the other end^17^ (Figure 1). Subjects are asked to point out their pain intensity on the VAS scale. Pain is evaluated, and measurement is carried out as the distance between “no pain” to the point where the patient marks on the scale.

**Figure 1 hsr2774-fig-0001:**

A 10 cm visual analog scale (VAS scale) marked as “no pain at all” and “pain as bad it could be,” and patients will be asked to point out the intensity of pain on the VAS scale.

### Off‐pump CABG

3.2

The first left internal mammary artery anastomosis to obtuse marginal (OM) was conducted in St Petersburg in 1964 by Kolessov and colleagues without using the heart–lung machine, hence called OPCAB.^18^ Instead of stopping the heart, technical advancements and new types of surgical equipment (intracoronary shunt, epicardial stabilizer) allow the surgeon to hold and stabilize the heart throughout the operation (Diagram 2).

**Diagram 2 hsr2774-fig-0003:**
[figure not shown]
Illustrates flow chart of study procedure. CABG, Coronary artery bypass graft surgery; ICU, intensive care unit; OPCAB, off‐pump coronary artery bypass; TEA, thoracic epidural analgesia; VAS, visual analog scale.

## LITERATURE REVIEW

4

Surgical stress, pain, and breathing difficulties contribute to the morbidity and mortality associated with heart surgery. Following cardiac surgery, pain disrupts the humoral and neuroendocrine systems' equilibrium, increasing stress hormone levels and myocardial oxygen demand.^5^, ^6^, ^7^, ^8^, ^9^, ^10^, ^11^, ^12^ As a result, arrhythmias and myocardial ischemia are increased. Pain also impairs mechanical ventilation and mobility restriction.^2^, ^10^, ^11^, ^12^, ^13^, ^14^, ^15^ Postoperative pain management in cardiac surgery has traditionally relied on pharmacologic therapy, either parenteral opioids or NSAIDs.^16^, ^17^, ^18^, ^19^, ^20^ However, they rarely provide analgesia comparable to a regional anesthetic.^21^ CABG surgery can be performed using a variety of regional anesthetic approaches. Thoracic epidural anesthesia should be preferred for thoracic surgeries due to its longer duration and advantage of prolonged postoperative pain management.^22^ However, the use of TEA decreased the incidence of myocardial infarction (MI), and it enhanced left ventricle (LV) function in patients undergoing aortic valve replacement alone or in combination with CABG, even when the left ventricular mass was increased.^23^

Cardiac surgery requires anticoagulants, and it is not widely accepted due to concerns about neuraxial hematoma following anticoagulants.^1^, ^14^, ^21^, ^22^, ^23^, ^24^, ^25^, ^26^ A few trials have demonstrated the safety of regional anesthetic and analgesic techniques in the context of possible anticoagulation during cardiac surgery.^1^, ^19^ Regional blocks have enormous potential to be integrated into hospitals' acute pain management paradigms following cardiac surgery, given their initial success in decreasing pain scores and reducing opiate usage.^26^

Spinal and epidural instrumentation entails risk, with epidural hematoma formation being the most feared complication.^25^, ^26^, ^27^, ^28^ Patients who did not receive thromboprophylaxis have a hematoma formation rate of one in every 220,000 spinal anesthesia cases and one in every 150,000 epidural anesthesia cases but in cardiac surgery, it is approximately 1:3552 observed by Landoni and colleagues.^27^, ^28^, ^29^ The VAS is frequently used to explore various subjective experiences, including pain. Subjects are asked to demonstrate severity by marking a 10 cm long horizontal line with the words “no pain” at one end and “worst pain conceivable” at the other end with a VAS. The essential advantage of VAS is that the ratings have the characteristics of ratio data and may be analyzed objectively as such, providing that the data are generally distributed. The VAS is applicable in a wide variety of clinical and testing situations.^30^, ^31^

Prospective, randomized research on postoperative pain following coronary artery bypass was conducted in Istanbul to determine the effects of thoracic epidural as an adjunct to general anesthesia. In the early postoperative phase after the CABG, TEA substantially decreased the severity of postoperative pain and the use of pain analgesics.^30^, ^31^, ^32^ Cardiac sympathectomy induced by TEA at spinal levels T1–T5 increases coronary flow and the balance of myocardial oxygen delivery and consumption and flow through the internal thoracic artery, the most commonly used conduit for coronary revascularization.^33^ Providing adequate perioperative analgesia has been shown to improve hemodynamics and immunologic responses, which may lead to improved outcomes after heart surgery.^26^

Thoracic epidural anesthesia combined with general anesthesia during OPCAB decreases the need for mechanical ventilation following surgery, decreases the length of stay in the intensive care unit (ICU), and provides better pain control than general anesthesia alone.^30^, ^31^, ^32^, ^33^ Furthermore, in a recent study, Mehta et al.^34^ observed combined efficacy of general anesthesia with TEA and observed better postoperative analgesia and clinical outcomes, especially cardiorespiratory and renal functions, and allowed first tract extubation following high‐risk cardiac surgery, similar to another European study findings conducted by Stenger et al.^35^ in Denmark. In this study, the authors aim to justify that the use of TEA shortens mechanical ventilation time and return of normal respiratory function, ICU stays, and provides stable hemodynamics compared to general anesthesia alone.^30^, ^31^, ^32^, ^33^, ^34^, ^35^

